
### 2.8. Strategies to Improve Study Adherence and Compliance

Several strategies will be established to maximize adherence and compliance with the study protocol. A booklet containing the food notebook and the questionnaires to be completed throughout the study will be provided to each eligible participant. This booklet will highlight the specific timings at which participants should fill out the questionnaires and record their food intake in an easy and convenient manner. Participants will be able to choose between three food menus, depending on their preferences. They will be provided with a box of easy-to-cook food items and a kitchen scale to facilitate meal preparation and the recording of food intake at their own home. In order to reinforce engagement in the study, the participants will receive reminder messages from the investigators. They will also have the possibility to communicate with the investigators through phone calls throughout the duration of the study. If necessary, they will be encouraged to ask questions and reminded of specific protocol instructions.

### 2.9. Data Management and Confidentiality

Each participant will be given a unique numerical/letter identifier, which will be used for all assessment documents. Data will be collected via paper and electronic database formats, in which only the participants’ unique identifiers will be used. Informed consent, with participants’ names, will be kept separately from the other documents in a locked filing cabinet by the principal investigator. A list of the participants’ names and their unique identifiers will be kept in a password-protected file, which will only be accessible to the research team involved in this project. After a period of 5 years, all documents mentioning the participants’ names will be shredded and disposed of safely. 

### 2.10. Statistical Methods

Statistical analysis and graphics will be performed using R Studio (version 4.0.5, RCore Team, 2021) and Prism 9 (GraphPad, San Diego, CA, USA). Continuous variables will be presented as means and standard deviations, subject to the normality of their distributions (using a Shapiro–Wilk test if necessary). In case of non-normality, they will be presented as medians, quartiles, and extreme values. Data manipulation, through logarithmic transformation, will only happen if violations of assumptions for each test are found. Non-parametric testing will be used if necessary: Friedman tests and Wilcoxon signed-rank tests for post hocs will be computed instead of one-way repeated ANOVAs; the Wilcoxon tests will replace the paired samples *t*-tests. As far as possible, graphic representations will be associated with these analyses.

#### 2.10.1. Statistical Analysis for Sleep Outcomes

For the sleep outcomes (TST, SOL, SE, WASO, REM, N1, N2, N3, and arousals), the differences between interventions (EED, MED, and DED) will be assessed using a repeated-measures ANOVA by comparing the three interventions as a within-subject factor. If significance is obtained, post hoc pairwise comparison tests with a Tukey HSD correction will be applied. Sleep measures during the interventions will also be compared to the baseline to evaluate the effect of each intervention separately, using paired samples *t*-tests. The effect sizes will be computed to assess the strength of the relationships: Cohen’s d for the *t*-tests and eta^2^ for the main effects.

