### 2.2. Participants

#### 2.2.1. Sample Size

An a priori analysis was conducted to establish the number of subjects needed to obtain a statistical power of 80%. Based on a repeated-measures design (four within the measures) for our primary outcome of interest (SE), it was found that 24 subjects would be required for the following parameters: alpha = 0.05, effect size f = 0.25 (medium effect), correlation among repeated measures = 0.5, and sphericity correction = 1. 

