### 2.7. Outcomes

#### 2.7.1. Primary Outcome: Sleep Efficiency

SE is defined as the ratio between total sleep time (TST) and total time spent in bed (TBT). It is given as a percentage. SE will be measured objectively during each session (i.e., CTL, DED, EED, MED) using an ambulatory polysomnograph (Sleep Profiler-PSG2, Advances Brain Monitoring, Carlsbad, CA, USA). The device is a portable multi-channel recorder that allows the acquisition of the following: the electroencephalographic (EEG), electrooculographic (EOG) and electromyographic (EMG) signals from three frontopolar channels; the airflow through a nasal cannula and pressure transducer; head movements and position by actigraphy; snoring, with an acoustic microphone; the pulse, using a forehead and finger sensor; the oximetry, using a wireless wrist oximeter; and the thorax and abdomen efforts by respiratory inductive plethysmography. The records will then be extracted through the Sleep Profiler portal. Validated auto-staging will be applied based on the ratios of the power spectral densities and the auto-detection of cortical and micro-arousals, sleep spindles, and ocular activity [40,41,42], which will be reviewed and modified by a sleep expert if needed. 

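### The three paired t-tests of sleep efficiency against the control session are neither gated nor corrected, so the chance of at least one false deficit effect on the primary outcome is about 12.7%, not 5%

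*Protocol article*

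**What the plan says.** Section 2.7.1 makes SE the primary outcome and has it recorded on all four nights: "SE will be measured objectively during each session (i.e., CTL, DED, EED, MED) using an ambulatory polysomnograph". Section 2.2.1 sizes the trial on those four nights, with "alpha = 0.05, effect size f = 0.25 (medium effect), correlation among repeated measures = 0.5, and sphericity correction = 1".

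Section 2.10.1 then tests SE, together with the other sleep outcomes, by two routes.

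- **Among the deficits.** Differences between EED, MED and DED "will be assessed using a repeated-measures ANOVA by comparing the three interventions as a within-subject factor". CTL is not in this model. The follow-up is conditional and corrected: "If significance is obtained, post hoc pairwise comparison tests with a Tukey HSD correction will be applied".
- **Against the control.** Sleep measures in the interventions are also "compared to the baseline to evaluate the effect of each intervention separately, using paired samples" t-tests. No preceding test has to be significant, and no adjustment is named.

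Section 2.10 gives the non-parametric substitutes: "Friedman tests and Wilcoxon signed-rank tests for post hocs will be computed instead of one-way repeated ANOVAs", and Wilcoxon tests in place of the paired t-tests. It names no adjustment for the latter. Nothing in the article says which SE test is the primary one or labels the contrasts with CTL as secondary or exploratory.

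**The concern.** The article deals with multiplicity explicitly for one family of SE tests and, in the next sentence, adds a second family without any control. The unprotected family matters more for the main objective in section 1.2, the acute effect of an energy deficit on sleep. The ANOVA omits CTL, so it can only show that the modalities differ from each other. If all three deficits shifted SE equally, it would have nothing to detect. A claim that some deficit changes sleep must come from the three t-tests, and any one of them at p < 0.05 would support it. What is at stake is the false-positive rate of that claim, which a reader of section 2.2.1 would take to be 5%.

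**Working it through.** **Inputs.** From section 2.2.1: n = 24, m = 4 measures, alpha 0.05, f = 0.25, correlation 0.5, sphericity correction 1, target power 80%. From section 2.10.1: a three-session ANOVA and three paired t-tests against baseline. Assumed: two-sided tests (sidedness is not stated), baseline means CTL, and no period or order effect.

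**1. The plan's own figure.** For a within-subject ANOVA, the noncentrality is f²·n·m/(1 − correlation), with (m − 1) and (n − 1)(m − 1) degrees of freedom.
- n = 24: 0.0625 × 24 × 4 / 0.5 = 12.0 on 3 and 69 df, power 0.817.
- n = 23: 0.0625 × 23 × 4 / 0.5 = 11.5 on 3 and 66 df, power 0.797.

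So 24 is the smallest n that reaches 80%. The figure reproduces, for a single test over four sessions at 0.05.

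**2. Bounds if the tests were independent.**
- Three tests: 1 − 0.95³ = 14.3%.
- Four tests: 1 − 0.95⁴ = 18.5%.

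**3. Allowing for the shared CTL night.** Simulation under no effect in any session, n = 24, equal correlations, 2,000,000 replicates:

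| Procedure on SE | Chance of at least one false positive |
|---|---|
| Three t-tests against CTL, each at 0.05 | 12.7% |
| The same, or the three-session ANOVA at 0.05 | 15.5% |
| Three t-tests with Holm (first step 0.05/3) | 4.5% |
| Holm on those three, or the ANOVA at 0.05 | about 8.5% |
| One four-session ANOVA | 5.0% |
| Tukey over all four sessions | 5.0% |

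Under no effect, Holm makes at least one rejection exactly when Bonferroni does, so the third and fourth rows hold for both. Repeat runs put the fourth row between 8.4% and 8.6%. Tukey tests among the deficits follow only a significant ANOVA, so they add nothing to the second row.

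**4. Sensitivity.** The rates do not depend on the common correlation (checked at 0, 0.5 and 0.8). With CTL residual variance half that of the other sessions, the first two rows become 13.6% and 15.8%. With double, they become 11.3% and 14.7%.

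**5. Power cost.** Let dz be the mean paired difference divided by its SD. If all three deficits lie the same distance d (in SD units) from CTL, then f = d × √(0.75/4) = 0.433d, so f = 0.25 gives d = 0.577. With correlation 0.5, dz = d/√(2 × 0.5) = 0.577. The noncentrality for one contrast is 0.577 × √24 = 2.83.
- At 0.05 (critical t 2.07, 23 df): power 77%; dz detectable with 80% power 0.60.
- At 0.05/3 (critical t 2.58, 23 df): power 60%; detectable dz 0.70.
- Tukey over four sessions (critical value 3.72/√2 = 2.63, 69 df): power 58%; detectable dz 0.71.

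**The case against.** The strongest reply is that section 2.10.1 asks two questions: whether the modalities differ, and what each does by itself. The hypothesis in section 3 favours exercise, which can be read as a between-modality question, and that family is controlled. On this view the contrasts with CTL are supporting analyses whose adjustment could be left to an analysis plan. Part of this stands. Counting the ANOVA and the t-tests as one family is a judgement, so 15.5% is conditional on it. The 12.7% does not depend on that choice, because it concerns the t-tests alone. The article also does not leave the matter open: it fixes a gate and a correction for one set of SE tests and neither for the other, without ranking them.

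Two stronger readings are tempting and are not supported.

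- A reader might infer that the Wilcoxon post hoc tests among the three deficit sessions also need Holm. If the gate in section 2.10.1 carries over to the Friedman test, which is the natural reading, they do not: with exactly three conditions, unadjusted pairwise tests after a significant overall test control the error by the closure principle. Simulation (n = 24, 100,000 replicates) gives 4.3% under no effect, and 3.3%, 4.7% and 5.0% with one session shifted by 0.5, 1 and 2 SD. The gap in the fallback is confined to Wilcoxon tests that replace the t-tests against CTL.
- A reader might infer that sharing one CTL night makes the error rate worse. It lowers it, from 14.3% to 12.7%. An atypical CTL night is a problem with the comparator, which no multiplicity correction addresses.

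The power cost is also a fair objection, the more so because section 3 describes the protocol as a pilot.

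**Conclusion.** The concern holds for the three SE contrasts with CTL. As written, the chance of at least one false deficit effect is about 12.7%, roughly two and a half times the alpha in section 2.2.1. It is about 15.5%, roughly three times, if the ANOVA is placed in the same family. Both figures assume two-sided tests at 0.05, no true effect in any session, equal correlations and no order effect. They also rest on reading baseline as CTL. The article uses the word for the run-in assessments too, but SE is specified for the CTL session, so that reading fits. This is a modest and easily corrected weakness in the inference on the primary outcome. It does not invalidate the design, and the contrasts among the deficits are adequately protected.

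**What to change.** For SE only, state that the three deficit-versus-CTL contrasts are tested with Holm, and that the same correction applies where Wilcoxon tests replace these t-tests. State that baseline means the CTL session.

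Holm alone does not restore 5% over all SE tests, because beside an ANOVA at 0.05 the total is still about 8.5%. If 5% overall is wanted, choose one of these before the data are analysed:

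- One repeated-measures ANOVA over all four sessions, with Tukey over all four (5.0%). This also matches the four-measure sample size calculation.
- Name one SE family as primary, either the contrasts with CTL or those among the deficits, and label the other secondary.

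Label the same contrasts on the other sleep outcomes as exploratory, with unadjusted confidence intervals.

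The change takes one or two sentences and no extra data. At the strictest Holm step, power at dz 0.577 falls from 77% to 60%, and the dz detectable with 80% power rises from 0.60 to 0.70. Later Holm steps cost less. Tukey over four sessions costs about the same as the first Holm step (58% at dz 0.577).

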## Abstract

Sleep is bi-directionally linked to energy balance. This crossover study design will evaluate the acute effect of a moderate energy deficit (500 kcal) induced by diet, exercise, or mixed (−250 kcal by diet and 250 kcal by exercise) on sleep and the next morning’s appetitive responses. The study sample comprises 24 healthy young adults. The experimental measurements will be conducted in a naturalistic, momentary manner and partly assessed by the participants. The participants will undergo a run-in period in order to stabilize their sleep schedules and provide them with training on the study protocol and measurements. Indirect calorimetry will be used to determine their resting metabolic rate and peak oxygen consumption (VO_2_ peak). Then, they will take part in a control session (CTL), followed by three energy deficit sessions in random order: a diet-induced energy deficit session (DED), an exercise-induced energy deficit session (EED), and a mixed energy deficit session (MED). All experimental sessions will be separated by a one-week washout. The participants’ sleep will be monitored by ambulatory polysomnography, and the next morning’s appetitive response will be evaluated via ad libitum food intake, appetite sensations, and food reward, measured by a food liking and wanting computerized test.

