### 1.2. Aims

The main objective of this study is to evaluate the acute effect of a moderate energy deficit (500 kcal) induced by diet, exercise, or both (mixed: −250 kcal by diet and 250 kcal by exercise) on the quality and architecture of sleep in healthy young adults. The secondary objectives will be to investigate the effect of the energy deficit modality on (i) next morning appetitive responses ([i_a_] ad libitum food intake, [i_b_] appetite sensations, [i_c_] food reward, (ii) sleepiness, and (iii) fatigue.

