## 2. Materials and Methods

### 2.1. Study Setting and Design

The “Exercise and/or Diet induced Iso-Energetic deficit effect on Sleep” (EDIES) is a single-center study with a crossover design in which each participant will be allocated to a randomized sequence of experimental sessions and, hence, acts as his own control. This trial will be conducted in Toulon, France (Toulon University, laboratory impact of physical activity on health [IAPS]), and received approval from an Institutional Review Board (IRB00012476-2023-28-02-235) with all undertaken assessments complying with the principles of the Declaration of Helsinki. The measurements are realized in a naturalistic, momentary manner and partly assessed by the participants in an ecological setting. The inclusion will be launched in March 2023, and a sufficient number of participants is expected to be reached within three months following the first inclusion.

Upon reception of the signed consent, the participants will undergo a run-in week. This will be followed by a control session (CTL), after which energy deficit sessions (diet-induced energy deficit session [DED], exercise-induced energy deficit session [EED], and mixed energy deficit session [MED]) will take place in random order. All experimental sessions (including the CTL) will be held for 28 h and separated by a one-week washout period (Figure 1).

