### 2.3. Randomization

#### 2.3.1. Sequence Generation

Upon reception of the signed consent, the participants will be subjected to a random allocation through a computer-generated list (created with “randomization.com”) (Kim and Shin, 2014). According to our within-subjects design, random permutations of interventions will be computed. Thus, each subject can be allocated to a specific order of interventions (any combination of EED, MED, or DED). The sequence allocation will be generated by the study’s statistician and provided to the investigators conducting the assessments. This document will be securely stored and password-protected on the University of Toulon’s online servers and only shared with the team members directly engaged in the study’s protocol.

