
### 2.5. Experimental Sessions

#### 2.5.1. Control Session

The control session (CTL) will be carried out over 28 h and starts when the participant wakes up (6:45 a.m.). Upon waking up, the participants will be equipped with accelerometers (GT3X+, ActiGraph LLC, Pensacola, FL, USA) on their waists until the next morning to monitor their physical activity. They will be asked to maintain their habitual overall level of physical activity, and any structured physical exercise during and 48 h before the session will be prohibited. Food intake will be organized over three scheduled meals (breakfast (7:15), lunch (12:30), and dinner (20:00)). The meals offered will be adapted to each participant’s preferences based on a panel of dishes proposed by the investigators (Table S2). The participants will be asked to take pictures of every consumed meal (habitual meal) and to fill out a food diary by weighing each consumed food item using a kitchen scale (EBC9i, EssentielB, Fretin, France) provided by the investigators. Appetite, sleepiness, and fatigue will be assessed throughout the day (i.e., 12 measures; Figure 2) using the Karolinska Sleepiness Scale (KSS) [33], Rating-of-Fatigue Scale (ROF) [34] and appetite visual analogue scale (VAS; 150 mm) [35], respectively. The Profile of Mood States questionnaire (POMS) [36] will be completed before bedtime. During the night, sleep will be measured by ambulatory polysomnography. The next morning, the participants will be asked to return to the laboratory in a fasting state. They will complete the Leeds Food Preference Questionnaire (LFPQ) [37,38] on a computer before being served a standardized ad libitum meal (buffet-style meal). After the meal, they will complete the LFPQ a second time. Sleepiness, fatigue, and appetite will be assessed throughout the morning (i.e., 8 measures; Figure 1). The control session will end at 10:35. 

The data collected during the control session will be used to assess the energy balance of each subject and to calibrate the food intake and exercises of the energy deficit sessions.

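### The control session always comes first, outside the random order, so the paired tests against it mix the effect of each deficit with time and cannot isolate it

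*Protocol article*

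**What the plan says.** The order is fixed in two places. The Abstract says "Then, they will take part in a control session (CTL), followed by three energy deficit sessions in random order", and section 2.1 says of the run-in week: "This will be followed by a control session (CTL), after which energy deficit sessions" take place in random order. Section 2.3.1 confirms what is permuted: "each subject can be allocated to a specific order of interventions (any combination of EED, MED, or DED"). CTL is not in the permutation.

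Section 2.5.1 gives the reason: "The data collected during the control session will be used to assess the energy balance of each subject and to calibrate the food intake" and the exercise of the deficit sessions.

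For sleep, section 2.10.1 plans two analyses. The first is a "repeated-measures ANOVA by comparing the three interventions as a within-subject factor", with CTL left out. The second is a set of paired t-tests: "Sleep measures during the interventions will also be compared to the baseline to evaluate the effect of each intervention separately". The word baseline is not defined there. CTL is the only reading that fits section 2.7.1, where "SE will be measured objectively during each session (i.e., CTL, DED, EED, MED"). Section 2.10.2 applies the same tests to mood, food preference, ad libitum intake and the areas under the curve.

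Section 2.1 counts CTL as an experimental session and says that each participant receives a randomised sequence of experimental sessions and so serves as his own control. Section 2.5.2 says that the deficit sessions differ from CTL in the 500 kcal deficit alone. The discussion in section 3 does not list the fixed order as a limitation.

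**The concern.** A participant is his own control in the useful sense only if the control condition can fall in any period. Here it falls in period 1 for everyone, and each deficit falls in periods 2 to 4 for everyone. Anything that changes between the first session and the later ones enters all three contrasts with CTL in the same direction. Candidates are residual adaptation to the recording device and familiarity with the buffet, the computer task and the rating scales.

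At stake is the absolute part of the main objective, to "evaluate the acute effect of a moderate energy deficit (500 kcal) induced by diet, exercise, or both". The three-way comparison shows whether the modalities differ. Whether any one of them improves or worsens sleep relative to no deficit is read from the tests against CTL.

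**Working it through.** **1. Plan's own figure.** Section 2.2.1 gives f = 0.25, four measures, correlation 0.5, sphericity 1 and alpha 0.05. With noncentrality f² × n × m / (1 − ρ) = 0.0625 × 24 × 4 / 0.5 = 12 on 3 and 69 degrees of freedom, power is 0.817; n = 23 gives 0.797. So 24 reproduces. That calculation does not address order.

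**2. What each contrast estimates.** Let τ be the effect of a deficit and π1 to π4 the period effects. With the three deficit orders balanced:

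- deficit minus CTL = τ + [(π2 + π3 + π4)/3 − π1]
- deficit A minus deficit B = τA − τB

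The bracket does not shrink with n. A period term cannot estimate it either, because CTL occurs only in period 1.

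**3. Illustration.** Inputs: n = 24 and ρ = 0.5 (section 2.2.1), two-sided 5% tests, no true effect. The bracket s, in SDs of a single night, is an assumption; the document gives neither a drift nor an SD for sleep efficiency.

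- SD of a paired difference = √(2(1 − ρ)) = 1 SD; standard error = 1/√24 = 0.204 SD
- noncentrality = s × √24; critical t on 23 degrees of freedom = 2.069
- the per-test rate is the upper tail of the noncentral t; the any-of-three rate is simulated, with the shared CTL

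| Assumed drift s | Noncentrality | False improvement, one test | At least one of three |
|---|---|---|---|
| 0 | 0 | 2.5% | 6% |
| 0.1 SD | 0.49 | 7% | 16% |
| 0.2 SD | 0.98 | 15% | 32% |
| 0.3 SD | 1.47 | 29% | just over 52% |

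The first row shows what multiplicity alone does; the rise below it is due to drift. At s = 0.25 SD the two-sided rate per test is 21.7%, ranging from 16.8% (ρ = 0.3) to 32.9% (ρ = 0.7). When CTL is simulated as balanced over four periods with the same 0.25 SD shift, the bias is zero and the per-test rate is about 4.5%.

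**4. Can a trend model rescue the contrast?** Fit a linear weekly trend over the three randomised sessions and extrapolate it to CTL, on average two steps back.

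- Step of 0.3 SD after the first session: the fitted slope is 0, so all 0.3 SD remains.
- Adaptation that halves each week, from −0.3 (then −0.15, −0.075, −0.0375): the bias is 0.3 − 0.0875 = 0.21. The slope is (0.15 − 0.0375)/2 = 0.056, so the correction is 0.11 and about 0.10 remains.
- Precision: the slope variance is 0.5/(2 × 24) = 0.0104; two steps multiply it by 4, giving 0.0417. Added to 1/24 = 0.0417 this is 0.0833, a standard error of 0.289 against 0.204, or 41% more.

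The correction is complete only if drift is linear.

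**The case against.** The best defence has four parts.

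- **The order has a reason.** CTL supplies the energy balance and the meals from which the deficit sessions are built (2.5.1, 2.5.2). This stands. It explains the order but does not remove the confounding. It also means that randomising CTL would not be a cheap change: a separate calibration day with weighed panel meals, activity monitoring and 48 hours without structured exercise would be needed.
- **The plan anticipates adaptation.** A run-in week stabilises the sleep window, checks compliance with accelerometers and familiarises participants with the device (2.4.1), and a habituation night is recorded (2.2.3). This stands as mitigation. It makes a large first-night effect less likely, but one week cannot exclude residual adaptation, and the document does not say that the buffet is practised beforehand.
- **The main comparison is sound.** The first analysis listed in 2.10.1 compares the three randomised conditions, and the hypothesis in section 3 is largely comparative. A reader might infer that the whole main objective depends on CTL. The document does not support that: differences between modalities are free of this bias.
- **The size is assumed.** This stands. A reader might also infer that the drift is known to favour exercise. That would need sleep to improve over sessions, and the document gives no evidence on direction. A downward drift would do the opposite.

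**Conclusion.** The concern holds for the deficit-versus-CTL contrasts and only for those. As designed, they cannot isolate the effect of each intervention, which is the purpose that 2.10.1 gives them. The statement in 2.5.2 that only the energy deficit differs does not hold against CTL, because period always differs as well.

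The confounding follows from the design and needs no assumption. Its size does: the false-improvement rates of 7%, 15% and 29% rest on assumed upward drifts of 0.1 to 0.3 SD, with the plan's n and correlation. If the run-in removed all drift, the rate would be the nominal 2.5%. The randomised comparison of the three deficits stands as planned.

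**What to change.** - In 2.10.1 and 2.10.2, name the randomised contrasts among the diet, exercise and mixed sessions as the basis for confirmatory conclusions.
- Define baseline as CTL. Report deficit-minus-CTL differences with confidence intervals as non-randomised, time-confounded estimates, without causal wording.
- In 2.1, say that only the three deficit sessions are in the randomised sequence. In 2.5.2, say that the deficit sessions differ from CTL in period as well as in energy deficit.
- Name the fixed order as a limitation in section 3.
- A linear trend extrapolated to the first session is optional. If used, report it as a sensitivity analysis valid only for linear drift, with the 41% larger standard error.

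The cost is wording and no new data. The downside is a weaker claim about each deficit against no deficit. The sample size should also be read accordingly: 2.2.1 assumes four measures, but the randomised ANOVA has three. With the same inputs its power at n = 24 is 0.741, and 28 participants would be needed for 80%. That gap exists in the plan already and is not created by this change.
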